## Abstract

**Background::**

Shunt-dependent hydrocephalus (SDH) is a well-known sequela following aneurysmal hemorrhage, adversely affecting the outcome after securing ruptured aneurysm. Fenestration of lamina terminalis (FLT) creates an anterior ventriculostomy, facilitates cerebrospinal fluid circulation and clot clearance in the basal cistern. However, controversy exists over whether microsurgical FLT during aneurysm repair can decrease the incidence of SDH.

**Aims::**

The study is designed to determine the efficacy of lamina terminalis fenestration on the reduction of SDH after aneurysm clipping.

**Methods/Design::**

A total of 288 patients who meet the inclusion criteria will be randomized into single aneurysm clipping or aneurysm clipping plus FLT in the Department of Neurosurgery, West China Hospital. Follow-up was performed 1, 3, 6, and 12 months after aneurysm clipping. The primary outcome is the incidence of SDH and the secondary outcomes include cerebral vasospasm, functional outcome evaluated by the modified Rankin Scale and Extended Glasgow Outcome Scale, and mortality.

**Discussion::**

The FISH trial is a large randomized, parallel controlled clinical trial to define the therapeutic value of FLT, the results of which will help to guide the surgical procedure and resolve the long-puzzled debate in the neurosurgical community.

**Conclusions::**

This protocol will determine the efficacy of FLT in the setting of aneurysmal subarachnoid hemorrhage.

**Trial registration identifier::**

http://www.chictr.org.cn/edit.aspx?pid=15691&htm=4

**Chinese Clinical Trial Registry::**

ChiCTR-INR-16009249.

## Background

1

Subarachnoid hemorrhage (SAH) is a major subset of cerebral hemorrhagic stroke with an annual incidence of 2 to 32 cases per 100,000 population.^[1]^ The vast majority of SAH (>85%) are caused by ruptured aneurysm.^[2,3]^ Aneurysmal SAH (aSAH) is a fetal condition with which 15% patients die on the spot,^[4]^ 40% within a month,^[5]^ only 55% patients are independent among survivors,^[4]^ and survivors of aSAH after 20 years showed 17% excess mortality compared with the general population.^[6]^ Surgical clipping to isolate the blood circulation of aneurysm cavity with parental artery is regarded as the treatment of choice although endovascular coiling with or without stent is getting popular.

Many a factors are associated with a poor outcome after aSAH, one of which is shunt-dependent hydrocephalus (SDH). In general, aSAH-induced hydrocephalus can be categorized as either acute or chronic considering the time course to presentation.^[7–9]^ Acute hydrocephalus occurs within hours mainly due to blockage of CSF flow^[8]^ while time of chronic hydrocephalus can vary from weeks to months and is not necessarily preceded by acute hydrocephalus.^[9]^ For patients with acute hydrocephalus, external ventricular drainage is performed to temporarily bypass cerebrospinal fluid. Most of these patients can tolerate clamping of the drainage at later stage during hospitalization while approximately 30% patients need permanent shunt.^[10,11]^ Meanwhile, the incidence of chronic hydrocephalus requiring shunt surgery was reported more than 20%.^[12–14]^ Therefore, SDH is a common complication following aSAH. According to the recent studies, the incidence of SDH after aSAH was around 20%^[13,15,16]^ ranging from 17.2% to 31.2%.^[17–19]^ Patients with SDH experienced higher mortality, worse short- and long-term prognosis with longer hospital stay.^[20,21]^ Moreover, SDH is an independent risk factor predicting long-term unfavorable functional outcome of aSAH.^[20]^

Traditionally, ventriculoperitoneal shunt is the treatment of choice after SDH. However, CSF shunts have high malfunction rates with reported 43% and 85% of shunts failure at 1 and 10 years after the first placement, respectively.^[22]^ Moreover, the procedure of shunt placement or revision has the risk of intracerebral hemorrhage,^[23]^ CSF leakage, infection, and bowel perforation or pneumothorax, with mortality up to 7% to 9% in selective populations.^[22,24,25]^ Specifically, although SDH after aSAH was considered less frequently to suffer shunt failure compared with other forms of hydrocephalus, 30% patients required a subsequent revision which contributed to multiple revisions.^[15]^

Fenestration of lamina terminalis (FLT) is a useful procedure during ruptured aneurysm surgical clipping to allow brain relaxation under increased intracranial pressure by offering free CSF flow from the third ventricle to the basal cistern. In addition, FLT has been performed to prevent the occurrence of SDH through facilitating CSF circulation, clearance of blood in basal cisterns, and improving CSF dynamics.^[8]^ Tomasello et al^[26]^ first assessed the effect of FLT in preventing SDH in 1999. Of the 52 patients included, only 2 (4.2%) patients developed SDH with a follow-up of 12 to 60 months. Since then, more than 400 patients were treated combining FLT, clot evacuation from the basal cisterns, and opening of the Liliequist membrane with the incidence of SDH less than 4%. Komotar et al^[27]^ in 2002 further confirmed the usefulness of FLT in a large population (582 cases) as they showed a decreased incidence of SDH in more than 80% patients with aSAH. Moreover, it was demonstrated that FLT was not also associated with reduced SDH, but also with decreased vasospasm and better outcome.^[28]^ Hence, FLT was recommended as a routine practice in patients with severe aSAH.^[27]^

However, the therapeutic role of FLT is questioned by recent studies. Komotar et al^[29]^ failed to observe decreased SDH as fenestrated patients had a shunt rate of 25% compared with 20% in unfenestrated patients. The negative results were supported by Chohan et al^[30]^ who intraventricularly injected a contrast agent to evaluate the functional patency of the fenestrated lamina terminalis with CT imaging, finding that contrast agent followed the normal ventricular pathway into fourth ventricle rather than in the basal cisterns. To define the controversial role of FLT, a systematic review including 11 studies involving 1973 patients was performed where no significant association between FLT and a reduced incidence of SDH was revealed with an overall incidence of 10%, 14% in the fenestrated and nonfenestrated cohort, respectively.^[13]^ However, the baseline data between the 2 cohorts were inconsistent, especially with more patients in poor clinical condition in the former. Actually, high grade SAH is a risk factor of the occurrence of SDH,^[17,18]^ so this difference reinforced the efficacy of FLT. Therefore, a well-designed randomized controlled trial is widely called on to definitively determine the efficacy of this technique.

To the best of our knowledge, only a single randomized controlled study was performed to address such debate.^[7]^ This clinical trial included 50 patients with ruptured anterior communicating aneurysm, suggested no significant difference between fenestrated and nonfenestrated group (24% vs 16%). However, more than 90% patients with low grade SAH and about 60% with Fisher grade I/II were included which underpowered to detect the difference as patients with low grade of H-H Grade or Fisher Grade are quite less likely to develop SDH. In addition, this study was obviously limited by the quite small sample size.

We designed this study to provide more robust evidence of the efficacy of FLT during surgical aneurysm clipping on the prevention of SDH with a large sample size and strict inclusion and exclusion criteria.

## Methods/design

2

### Study design

2.1

The FISH trial is a prospective, single-center, parallel, randomized, assessor-blinded trial. The overall flowchart is demonstrated in Figure 1. The main objective is to compare the incidence of SDH in the patients undergoing aneurysm clipping plus FLT or not. The secondary aim is to determine the effects of FLT on vasospasm within 1 month and functional outcome within 1 year in patients with anterior circulation aneurysm.

**Figure 1 F1:**
[figure not shown]
Flow chart of the clinical trial. AC = aneurysm clipping, EGOS = extended Glasgow outcome scale, FLT = fenestration of lamina terminalis, mRS = modified Rankin Scale, SDH = shunt-dependent hydrocephalus.

### Ethics approval and consent to participate

2.2

This study will be conducted at the Department of Neurosurgery of West China Hospital, Sichuan University. The clinical trial has been approved by the Biological and Medical Ethics Committee (BMEC) of West China Hospital (2016-No.197) and has been registered in the Chinese Clinical Trial Registry (ChiCTR-INR-16009249). All patients or their relatives will be fully notified including the potential benefits and risks of this trial (Fig. 2) and informed consent will be achieved. Withdrawal from the trial is allowed at any point without any constraint for each subject.

**Figure 2 F2:**
[figure not shown]
The potential risks and benefit of FISH.

### Recruitment, randomization, and blinding

2.3

#### Recruitment

2.3.1

West China Hospital is a 4300-bed, superior large comprehensive researching and teaching hospital in China. Our neurovascular center consists of 5 special teams and more than 600 aneurysm surgical clipping are performed annually. All potential subjects in hospital are encouraged to participate in the FISH trial. Because of the sufficient patients’ resources, adequate participant enrolment to reach target sample size is expected within 1 year at most.

#### Randomization

2.3.2

Patients will be allocated to either single aneurysm clipping group or aneurysm clipping plus FLT group by the minimization method that is performed by a minimization software. The stratification factors for minimization include age, Fisher grade, admission GCS, and acute hydrocephalus. Once a patient is qualified, the baseline information including demographics, medical history, time from SAH onset, Hunt–Hess grade, Fisher grade, and physical examination of the patient will be sent to a special researcher who is in charge of patients randomization.

#### Blinding

2.3.3

In this trial, because both the patients and doctors cannot be blinded, the assessor must be blinded to guarantee the research quality. Other measures are further adopted. First, the outcomes will be evaluated by 2 independent investigators who participate in neither the allocation nor the treatment and the final results will be filled in electronic case reports forms (CRF) without any modification once they are confirmed. Second, patients and related medical staff will be instructed not to leak any information regarding the treatment before and during the outcome evaluation. In addition, a statistician who will perform the statistical analysis is not allowed to take part in the implementation of the clinical trial (Fig. 2).

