### Intervention

2.5

Patients allocated in the control group will undergo standard microsurgical aneurysm clipping via pterion approach within 3 days after stroke onset. Sharp dissection of sylvian cistern, and then carotid, chiasmatic cisterns will be made to decrease intracranial pressure and expose the aneurysm according to the preoperative angiography. The Liliequist membrane will also be opened. The neck of aneurysm is seen clearly and clipped correctly avoiding the near perforating artery occlusion and parental artery narrowing under microscope of high resolution. The subarachnoid clot around the basal cistern will be meticulously cleared away. We do not routinely perform ventriculostomy that is reserved for patients with decreased consciousness and acute hydrocephalus.

Patients in the interventional group will undergo an additional fenestration of laminal terminalis after the same aneurysm clipping procedure. FLT will be performed in the following steps: a self-retaining retractor adjusted parallel to the anterior communicating artery to completely expose the lamina terminalis that is a bluish, bulging membrane behind the optic chiasm; an incision about 5 mm in length made strictly in the midline of the lamina terminalis to avoid injury to the adjacent neurovascular structures; the opened rim briefly coagulated to avoid subsequent reclosure as a result of adhesions. Postoperatively, standard medical treatment will be used in accordance with the recommendation of the professional guideline.

The trial will be terminated in advance if apparent benefit or higher rate of severe AE in one of the 2 interventions is revealed at a high significance level that is defined as differences of more than 3 standard deviations. To improve the adherence of protocol intervention, surgeons are not allowed to change the interventional strategy once the randomized grouping is determined. In addition, the video record of the entire surgical process will be checked at random to monitor the consistency of intervention. External CSF drainage is prohibited during the operation in the trial.

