#### Primary outcome

2.6.1

The primary outcome of this trial is the incidence of shunt-dependent hydrocephalus confirmed by both clinical symptoms and CT scan at 1 year after operation. Clinical manifestation includes a progressive decline in neurological function (deterioration of mental status, urinary incontinence, gait disturbance, and memory impairment). The radiographic diagnosis of hydrocephalus is made on the basis of the ventriculomegaly with the following observations: enlarged frontal and temporal horns, enlargement of the third ventricle, a narrowed pattern of cortical sulci, and the presence of periventricular oozing. Ventricular size is determined by the cerebral ventricular index (the greatest width between the frontal horns at the level of the Monro foramen divided by the transverse inner distance of the cranium at the same level).^[26]^ Radiologically, hydrocephalus is diagnosed when the ventricular size exceeds the 95th percentile after adjusting for patient age. Whether or not shunt is placed depends on the following criteria: ventricular enlargement on radiological imaging stated above, the progressive neurological dysfunction, and the consequent improvement after lumbar drainage.^[31]^

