### Data collection and management

2.8

The trialist who specializes in randomization will store the allocation data and neurosurgeons will fill in CRF. The follow-up information form must be separately finished by another 2 investigators who have been trained eligible for outcome evaluation. We will use double input method for the data entry and the database will be inspected by the Quality Monitoring Board (QMB) and the principal investigator, then be locked up and sent to the statistician.

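### The plan declares patients unblindable although the arms differ only by a small internal step, leaving symptom reports and, by inference, the shunt decision exposed to knowledge of the allocation

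*Protocol article*

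**What the plan says.** The Study design section (2.1) labels the trial: "The FISH trial is a prospective, single-center, parallel, randomized, assessor-blinded trial". The Blinding section (2.3.3) explains that "because both the patients and doctors cannot be blinded, the assessor must be blinded to guarantee the research quality". It adds three safeguards: two independent investigators, outside allocation and treatment, evaluate the outcomes; patients and staff are told not to disclose the treatment around the evaluation; and the statistician takes no part in running the trial.

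The Intervention section (2.5) describes the arms. For control: "Patients allocated in the control group will undergo standard microsurgical aneurysm clipping via pterion approach within 3 days after stroke onset". For the experimental arm: "Patients in the interventional group will undergo an additional fenestration of laminal terminalis after the same aneurysm clipping procedure". The added step is a midline incision of about 5 mm in the lamina terminalis.

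The Primary outcome section (2.6.1) states: "The primary outcome of this trial is the incidence of shunt-dependent hydrocephalus confirmed by both clinical symptoms and CT scan". The symptoms are "deterioration of mental status, urinary incontinence, gait disturbance, and memory impairment". The CT part uses a ventricular index compared with an age-adjusted 95th percentile. Shunt placement rests on that enlargement plus "the progressive neurological dysfunction, and the consequent improvement after lumbar drainage". The section does not say who makes the decision.

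Data collection and management (2.8) says that "neurosurgeons will fill in CRF", and that two other trained investigators complete the follow-up form separately.

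**The concern.** An assessor-blinded design is reasonable when patients cannot help knowing what was done to them. Here the described difference lies inside the skull, is made under the same operation and leaves no described outward sign. The plan therefore gives up patient blinding without a stated reason and relies on the discretion of people who know the allocation. Some of those patients will have the impaired memory or mental status that the endpoint is meant to detect.

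The primary outcome is at stake. Half of its definition is clinical symptoms, which depend partly on what patients and relatives report. Shunting also depends on judged decline and on response to lumbar drainage. If knowledge of the arm changes what is reported, or when a patient is tested, that has already happened when the blinded assessor sees the case, and no later analysis can undo it.

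**Working it through.** **Step 1: is patient blinding impossible?** Sections 2.3.3 and 2.5, side by side:

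| Element | Control | Clipping plus fenestration |
|---|---|---|
| Approach | Pterional | Same |
| Cistern dissection, Liliequist opening, clot removal | Yes | Same |
| Fenestration, about 5 mm, internal | No | Yes |

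Nothing that a patient or relative could see or feel is described as different. The operating team must know the allocation. Nothing in the article requires patients or relatives to know it.

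**Step 2: who makes the judgements behind the outcome?** Section 2.6.1 names nobody for the lumbar drainage or the shunt. Section 2.3.3 keeps the two assessors out of treatment. A shunt is treatment, so by inference the decision falls to treating doctors, whom the same section declares unblinded. This is an inference from two sections, not a statement in either.

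**Step 3: what do the safeguards cover?** Blinded evaluation and the separate follow-up form protect the assessors' own rating. The ventricular index protects the imaging part. Neither covers symptoms as reported by a patient who knows the arm, nor a drainage test or shunt that has already been done or not done.

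**Step 4: how sensitive is the comparison to a shift?** The article gives no figure for such a shift, so there is nothing to reproduce, and what follows is illustration only. Section 2.6.3 has 144 per arm with 10% loss: 144 × 0.9 = 129.6, taken as 130 or 129. Assume no true effect and a two-sided test at 0.05.

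With recorded rates p1 and p2, n per arm and p̄ their mean:

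- s0 = √(2p̄(1 − p̄)/n)
- s1 = √(p1(1 − p1)/n + p2(1 − p2)/n)
- P(reject) ≈ Φ((|p1 − p2| − 1.96·s0)/s1)

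For 17.5% against 12.5% with n = 130: s0 = 0.0443 and s1 = 0.0442, so (0.05 − 0.0868)/0.0442 = −0.83 and Φ = 0.20.

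| Assumed recorded rates | n per arm | Shift (points) | P(falsely significant) |
|---|---|---|---|
| 16.5% v 13.5% | 130 | 3 | about 10% |
| 17.5% v 12.5% | 130 | 5 | about 20% |
| 19% v 11% | 130 | 8 | about 44% |
| 20% v 16% | 129 | 4 | about 13% |
| 20% v 14% | 129 | 6 | about 25% |
| 20% v 10% | 129 | 10 | about 61% |

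With no shift the rate is 5%. The first three rows keep the mean at 15%. The last three start from the 20% control rate in section 2.6.3 and move one arm only.

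**The case against.** The plan openly declares an assessor-blinded design and supports it. Two investigators outside allocation and treatment evaluate the outcomes and complete their own follow-up form, and confirmed results are not altered. The imaging criterion is measured, and shunting is tied to criteria set in advance, which limits shunting on belief alone. The operating surgeon cannot be blinded. The article also condenses a fuller protocol, which may name who decides on shunts. All of this stands, and it lowers the weight of the point. It does not explain why patients must know their arm, and it does not prevent delayed or reduced testing in one arm.

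A reader might go further in four ways that the document does not support:

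- **That treating doctors are stated to order the drainage and decide on the shunt.** This is only inferred.
- **That the neurosurgeons' case report form carries the primary outcome.** The separate follow-up form in section 2.8 speaks against that.
- **That any bias must favour fenestration.** The Background reports opposed findings, including shunt rates of 25% against 20% and 24% against 16% to the disadvantage of fenestration, so clinicians' expectations may run either way.
- **That all ward and follow-up doctors can be blinded at no cost.** The article does not show that postoperative care is separate from the operating team.

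**Conclusion.** The point holds in a limited form. The statement that patients cannot be blinded has no support in the article's own description of the two operations. As a result, an avoidable route to bias in the symptom part of the primary outcome stays open. A second route, through the shunt decision, is probable but rests on inference.

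Neither the size nor the direction of the effect can be derived from the document. The 10% to 61% range above depends on shifts chosen for illustration. It shows only that a difference of a few percentage points in how cases are reported or tested would multiply the nominal 5% error rate.

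This is a design weakness with real mitigations already in place, not a contradiction that invalidates the trial. It should be fixed, because the remedy is cheap and most of it cannot be applied once patients have been told their arm.

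**What to change.** 1. In section 2.3.3, replace the statement about patients: patients and relatives are not told the allocation, and an emergency unblinding route exists.
2. Keep the allocation from postoperative staff outside the operating team where existing staffing allows. Use a neutral entry in the operation note, with the detail held by the researcher in charge of randomization.
3. Have the two existing independent investigators apply the criteria already in section 2.6.1 to CTs and clinical extracts masked to allocation. The material should come from the 1, 3, 6 and 12 month visits and from any shunt episode. Use their verdict as the primary outcome.
4. Report by arm any shunts placed without a blinded indication. Report also how many patients had lumbar drainage tried, because its result is unavailable to the assessors where it was not tried.

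**Cost:** protocol wording, handling of the operation note, preparation of masked extracts and the unblinding route. The two assessors already exist. Blinding postoperative doctors may need a staffing separation that the article does not establish, so that part is conditional. No clinical criterion changes.

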### Eligibility criteria

2.4

#### Inclusion criteria

2.4.1

1.Age ≥40 years but less than 70 years;2.SAH confirmed by head CT scan or lumbar puncture;3.Computed tomography angiography (CTA) and digital subtraction angiogram (DSA)-proved diagnosis of anterior circulation aneurysm;4.Admission within 72 hours from stroke ictus;5.SAH is graded as Fisher grade 3–4 on admission by initial CT scan;6.Clinical symptoms categorized as Hunt–Hess grade 3–4;7.Signed informed consent.

